# METHODOLOGY

## STUDY DESIGN

This project involves a double-blinded, randomized, non-inferiority trial in children 2-59 months of age from a malaria-endemic setting in Malawi comparing the effectiveness of 3-day to 5-day amoxicillin DT treatment for chest-indrawing, community-acquired pneumonia (ITIP2).

We plan to evaluate treatment with 3 days versus 5 days of oral amoxicillin DT in two divided doses based on age bands (500 mg/day for children 2 months up to 12 months, 1000 mg/day for children 12 months up to 3 years, and 1,500 mg/day for children 3 years up to 5 years of age) among 2,000 children presenting with chest-indrawing pneumonia in a malaria-endemic region of Malawi. Children in the 3-day arm will also receive 2 days of placebo following 3 days of active drug to complete a 5-day course to maintain the blind as to their randomization allocation.

## STUDY SITE

The Save the Children (SC) PI; the local co-PIs, from the College of Medicine (COM) at the University of Malawi and the University of North Carolina (UNC) Project, Lilongwe Medical Relief Fund Trust; and the team of co-investigators will conduct the research at Kamuzu Central Hospital (KCH) in Lilongwe. A 750-bed government facility, KCH is the primary referral hospital for the central region of Malawi, serving a population of approximately 5 million. Up to 30 or 40 children 5 years of age or younger with fast-breathing pneumonia are seen each day in the outpatient department (OPD) at KCH during the peak pneumonia season. The KCH pediatric department alone admits around 22,000 children per year. Over 100 children 5 years or age or younger with chest-indrawing pneumonia are admitted on average each month at KCH, with as many as 260 admissions a month during peak pneumonia season.

One of the major medical training institutions in Malawi, KCH has four full-time on-call pediatricians, two part-time pediatricians, three medical officers, three to six medical interns, 12 full-time clinical officers, and 45 nurses on staff. In the OPD, two to three clinicians with the support of two to three health surveillance assistants manage the triage area. In addition to the triage area, there are also emergency/resuscitation, priority, and low-risk areas in the OPD. The hospital has a high-functioning laboratory unit and a radiology unit that is capable of conducting x-rays (including a mobile unit, which is housed in the pediatric ward), ultrasounds, and computed tomography scans.

Bwaila District Hospital (BDH) is the district hospital for Lilongwe and is located in the central business district of Lilongwe. Approximately 200 to 250 children present to the BDH OPD per day. There are no inpatient facilities for children at BDH, and those requiring inpatient care are referred to KCH.

## STUDY POPULATION

## Study Population Overview

Although KCH draws from a large catchment area in the central region of Malawi, children eligible for this study are to be from the Lilongwe District. Malawi is ranked 174th in the United Nations Development Programme’s human development index, and almost 89% of the working population earns less than $2USD a day.[9] Lilongwe includes large peri-urban settlements with crowded living conditions and without adequate sanitation infrastructure. Overall, the nation’s adult literacy rate is 61%. Life expectancy at birth is 55.31 years and the under-five mortality rate is 71 deaths per 1000 children.

Malaria is endemic in Malawi with the highest prevalence of malaria parasitaemia in children between 6 and 36 months of age (60.1%).[10] The incidence of malaria in the area is highest during the rainy season, between December and April each year. Malawi’s adult HIV prevalence was estimated to be 10.3% in 2013. There were 170,000 estimated HIV-positive children 14 and younger. HIV is more prevalent in urban communities than rural areas.[11]

We expect study participants to be representative of the ethnic demographics in the area. We anticipate enrolling equal numbers of female and male children for a total participant population of 2,000 volunteers for this trial.

## Participant Eligibility

Study participants will be HIV-1 seronegative children 2-59 months of age who present to KCH or BDH with chest-indrawing. Volunteer families will be recruited and screened, those whose children are determined to be eligible, based on the inclusion / exclusion criteria, will be enrolled in the study and followed for 14 days. Recruitment, screening and enrollment can occur at KCH or BDH. Hospital observation or admission, and follow-up will occur at KCH. Final eligibility determination will depend on the results of the medical history, clinical examination, appropriate understanding of the study and completion of the consent process.

Case definition of chest-indrawing pneumonia:

- - Cough <14 days or difficulty breathing
  - Visible indrawing of the chest wall, with or without fast-breathing

## Inclusion Criteria

- - Male or female, 2 to 59 months of age.
  - History of cough <14 days or difficult breathing with chest-indrawing.
  - Ability and willingness of child’s caregiver to provide informed consent and to be available for follow-up for the planned duration of the study, including accepting a home visit if he/she fails to return to KCH for a scheduled study follow-up visit.

## Exclusion Criteria

- If chest-indrawing observed at screening resolves after bronchodilator challenge, among those with wheeze at screening.
- Severe respiratory distress (e.g., grunting, nasal flaring, head nodding, or severe chest-indrawing).
- Presence of WHO IMCI danger signs including: lethargy or unconsciousness, convulsions, vomiting everything, or inability to drink or breastfeed.
- Hypoxia (SaO2 < 90% on room air, as assessed by a Lifebox pulse oximeter).
- Stridor when calm.
- HIV-1 seropositivity or HIV-1 exposure, assessed as follows:
  - An HIV-positive result upon rapid antibody test will exclude any child from this study.
  - If a child is less than 12 months or age with a positive rapid test result, the child will be referred to receive additional confirmatory HIV testing (e.g., dried blood spot filter paper test) and follow-up from KCH staff, as per standard of care. Even if the confirmatory HIV testing subsequently shows that child is HIV-negative, he or she will remain excluded from the study.
  - If a child is less than 24 months of age and has an HIV-negative result upon rapid antibody test, the child’s biological mother’s HIV status will need to be assessed. If the mother is HIV-positive, the child will be excluded. If the mother has a documented HIV-negative test result from within the past 6 weeks, the child will be included. If the mother does not have documentation of an HIV-negative test result, she will be tested via rapid antibody testing to determine the child’s eligibility for this study.
  - If a child is over 24 months of age, an HIV-negative rapid antibody test is required for inclusion in the study.
  - Note: If a child has documentation of an HIV-negative test result from within the past 6 weeks, that test result will be used for the child’s eligibility assessment according to the algorithm described above.
- Severe acute malnutrition (i.e., weight for height/length < -3 SD, mid-upper arm circumference <115 mm, or edema).
- Possible tuberculosis (coughing for more than 14 days).
- Severe anemia, classified by WHO pocketbook guidelines (i.e., severe palmar pallor or hemoglobin <8.0 g/dL)
- Severe malaria, classified by WHO pocketbook guidelines (e.g., positive mRDT with any danger sign, stiff neck, abnormal bleeding, clinical jaundice, or hemoglobinuria)
- Known allergy to penicillin or amoxicillin.
- Receipt of an antibiotic treatment in the 48 hours prior to the study based on caregiver’s self-report and/or documentation in child’s medical record.
- Hospitalized within 14 days prior to the study.
- Living outside Lilongwe urban area, the study catchment area.
- Any medical or psychosocial condition or circumstance that, in the opinion of the investigators, would interfere with the conduct of the study or for which study participation might jeopardize the child’s health.
- Any non-pneumonia acute medical illness which requires antibiotic treatment per local standard of care.
- Participation in a clinical study of another investigational product within 12 weeks prior to randomization or planning to begin participation during this study.
- Prior participation in an Innovative Treatments in Pneumonia study during a previous pneumonia diagnosis.

## STUDY PERIOD

Each child will be followed for 14 days after enrollment. Projected duration of enrollment is anticipated to be about 30 months for this study. The high volume of children presenting to the OPD each day with pneumonia is expected to exceed the capacity of study staff to adequately assess each child for this study, so a maximum of 15 children for this trial will be enrolled each day. To avoid potential selection bias, each day children will be screened for enrollment in a sequential manner, as much as possible. Children that are not assessed for this study will receive the standard of care at KCH or BDH, which includes 5 days of oral amoxicillin, hospitalization, and treatment of any co-infection.

The funding for this study is for three years. This period includes the time required to prepare the necessary documents for the study, train all study personnel, initiate the study site, conduct the study and all data collection procedures, clean and analyze the data, and prepare the results for publication and presentation.

## SAMPLE SIZE

Refer to Section 5, Statistical Design and Analysis, for more details.

A total of 2,000 children (1,000 per treatment group) will be enrolled. With this sample size we aim to rule out a relative increase in failure rate of 50%. The power of the study to show non-inferiority of the 3-day treatment group at the final analysis when both treatment groups have exactly the same failure rate depends on the failure rate in the standard treatment (5-day) group. The estimated power is adjusted for a 5% loss to follow-up rate in each of the arms. For example, with 1,900 children (950 per treatment arm) for the primary analysis this study has 88% power to show non-inferiority of the 3-day treatment group if the failure rate in both groups is 8% and the non-inferiority margin is a 50% relative increase (which for this failure rate is equivalent to an absolute non-inferiority margin of 4.0%). For this failure rate in the standard treatment group (of 8%), at the final analysis the 95% confidence interval would exclude 12.0%, even if the failure rate is as large as 9.7% in the 3-day treatment group. With 1,900 children with complete outcome data in the primary analysis, the power of this study to show non-inferiority ranges from 64.8% if the failure rates in both groups are 4%, to 96.5% if the failure rates in both groups are 12% (assuming a relative non-inferiority margin of 50% (or equivalently a factor of 1.5). Further details will be provided in the Statistical Analysis Plan (SAP).

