## Analytical Methodology for Interim Analyses

For the chest-indrawing cohort, we plan two interim analyses after about one-third and two-thirds of children have been enrolled. We assume a one-sided test with an alpha=0.025, sample size=1900 (assuming 5% loss to follow-up in each of the arms), a Pocock design for early inferiority and O’Brien-Fleming for early non-inferiority stopping boundaries and a 1.5% relative difference failure rate between treatment (3-day) and control (5-day amoxicillin). The DSMB will consider recommending to stop the study prior to maximum enrollment if they determine early non-inferiority, early inferiority, or safety concerns. Details of the sequential monitoring plan will be finalized in collaboration with the DSMB and provided in the Statistical Analysis Plan (SAP).

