2. Proportion of children with either treatment failure or clinical relapse before or on day 14 (among all randomized children).
3. Proportion of children with AEs and SAEs.
4. Proportion of children with treatment failure among those testing positive for malaria by rapid diagnostic testing (mRDT) at baseline (overall).
5. Proportion of enrolled children failing treatment among those with wheeze during screening (identified prior to administration of bronchodilators).
6. Proportion of enrolled children failing treatment among those with oxygen saturation <93% by pulse oximetry at baseline.
7. Proportion of children failing treatment among those with MUAC-defined moderate malnutrition (11.5-13.5cm).
8. Proportion of children failing treatment among those with very fast-breathing for age (>70 breaths per minute for 2–11 months, >60 breaths per minute for 12–59 months).
9. Proportion of children failing treatment by age at baseline.
10. **STATISTICAL METHODOLOGY**

*7.1 Design*

The study will include 2,000 children aged 2 to 59 months. Children will be randomized to receive oral amoxicillin for 5 days (control) or 3 days + 2 days placebo (treatment). Treatment will be block randomized (with concealed block size) to ensure a 1:1 ratio of intervention and control. Randomization will be stratified by age group (2 up to 12 months, 12 up to 3 years, 3 years up to 5 years) and site (Bwaila District Hospital and Kamuzu Central Hospital).

*7.2 Interim analysis* We planned two interim analyses after about one-third and two-thirds of children have been enrolled. The seqDesign[2] software was used to determine the appropriate non-inferiority and futility stopping boundaries at each analysis. We assumed a one-sided test with an alpha=0.025, sample size = 1900 (assuming 5% loss to follow-up in each of the arms), a Pocock design for early inferiority and O’Brien-Fleming for early non-inferiority stopping boundaries and a 1.5 relative non-inferiority boundary.

The maximum true failure rates at both the interim analyses and final analysis for the 3-day group for which the 95% CI excludes the non-inferiority margin for various 5-day treatment group failure rates are provided in Table 1 below.

Table 1. Maximum true failure rates for the 3-day treatment arm beyond which stopping for early non-inferiority will be considered

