| 5-day failure rate | Non-inferiority bound | Max 3-day failure rate, 1st interim analysis | Max 3-day failure rate, 2nd interim analysis | Max 3-day failure rate, final analysis |
| --- | --- | --- | --- | --- |
| 7.0% | 10.5% | 4.0% | 7.2% | 8.3% |
| 8.0% | 12.0% | 5.0% | 8.5% | 9.7% |
| 9.0% | 13.5% | 6.0% | 9.8% | 11.0% |
| 10.0% | 15.0% | 7.1% | 11.1% | 12.4% |
| 11.0% | 16.5% | 8.2% | 12.4% | 13.7% |
| 12.0% | 18.0% | 9.4% | 13.7% | 15.1% |

The minimum true failure rates for the 3-day treatment group for which futility is considered for various 5-day treatment group failure rates are provided below.

Table 2. Minimum true failure rates for the 3-day treatment arm where futility will be considered

| 5-day failure rate | Min 3-day failure rate, 1st interim analysis | Min 3-day failure rate, 2nd interim analysis | Min 3-day failure rate, final analysis |
| --- | --- | --- | --- |
| 7.0% | 10.2% | 8.9% | 8.3% |
| 8.0% | 11.7% | 10.3% | 9.7% |
| 9.0% | 13.2% | 11.7% | 11.0% |
| 10.0% | 14.6% | 13.1% | 12.4% |
| 11.0% | 16.1% | 14.5% | 13.7% |
| 12.0% | 17.6% | 15.9% | 15.1% |

Figure 1 shows the maximum true failure rate in the 3-day treatment group in reference to various possible failure rates in the 5-day treatment group and a 1.5 relative non-inferiority margin (50% relative increase in failure rate) that would result in a 95% confidence interval at maximum enrollment which excludes the non-inferiority margin. The figure also indicates the power the study has to show non-inferiority if the failure rates are exactly the same in the two treatment groups for various possible failure rates. Of note, the estimated power is adjusted for a 5% loss to follow-up rate in each of the arms. This is considered conservative with respect to the multiple imputation procedure that will be used to account for missing outcome values.

**Figure 1.** Chest-indrawing pneumonia failure rates

Note:

- Blue, solid circles, blue number below: Potential failure rates for the 5-day treatment group.
- Blue, solid circles, blue number above: Power to detect the alternative of exactly equal failure rates in both treatment groups
- Green, hollow squares: Non-inferiority margins (depending on assumed failure rate in the 5-day treatment group.

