Hollow, red circles: Maximum true failure rate for the 3-day treatment group observed at maximum enrollment of 2,000 children (1,000 children in each control and treatment groups and assuming 5% loss to follow-up in each of the groups resulting in 1,900 children with complete outcome data for the primary analysis) for which the 95% confidence interval excludes the non-inferiority margin. For example, for a failure rate of 8% in the 5-day treatment group (assumed for the chest-indrawing pneumonia), the true failure rate in the 3-day treatment group can be 9.7% (1.7% above the control group) and can still rule out with high confidence a failure rate of 12% in the 3-day treatment group.

The DSMB will consider recommending to stop the study prior to maximum enrollment if they determine early non-inferiority, early inferiority, or safety concerns.

Early non-inferiority will be considered if the 3-day failure rate is lower than the rates provided in Table 1 for a given 5-day treatment failure rate. For instance, if the 5-day treatment rate at the first interim analysis is 7%, then early non-inferiority will be considered if the 3-day failure rate is less than 4.0%.

Early futility will be considered if the 3-day failure rate is higher than the rates provided in Table 2 for a given 5-day treatment failure rate. For instance, if the 5-day treatment rate at the interim analysis is 7%, then early futility will be considered at the first interim analysis if the 3-day failure rate is higher than 10.2%.

- 1. *Final analysis*

For the primary outcome, we will estimate the failure rate difference and 95% CI between the 3-day and 5-day amoxicillin DT treatment groups after adjustment for age, 2 up to12 months, 12 months up to 3 years, 3 years up to 5 years, site (Bwaila District Hospital and Kamuzu Central Hospital) and gender (precision variable[1]). Since estimates are expressed in rate differences we will run a linear regression model with treatment arm as predictor (3-day vs. 5-day), failure rate (yes vs. no) as outcome and age, site and gender as covariates using robust standard errors and calculate a 95% CI. We will use a 1.5 relative non-inferiority margin. If the failure rate in the 5-day arm is 7%, the non-inferiority margin will be 10.5% (=7%*1.5). With a 5% failure rate the non-inferiority margin will be 7.5% (=5%*1.5).

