To account for anticipated loss to follow-up or study withdrawal we will use multiple imputations for any missing outcome data. We will then perform sensitivity analyses to assess how the results might change with varying imputation assumptions. More information is provided in section 8 below.

1. **HANDLING OF MISSING DATA AND OTHER DATA CONVENTIONS**

We have estimated that loss to follow-up or study withdrawal will be 5%. Children lost to follow-up cannot be classified as improved or treatment failures at the missed visit. We will use multiple imputations for any missing outcome data. The imputations will be performed separately for each treatment group and cohort using multiple (20) hotdeck imputations and other information as described below. Multiple imputation estimates will be combined using Rubin’s approach[3].

Specifically, for each episode that is missing outcome data, we will create a subset of episodes that match exactly on treatment arm and gender while matching on age category, highest educational level achieved by the mother (none, primary, secondary, tertiary, while combining these categories for categories with less than 5% of participants, if needed, unknown education level will be multiply imputed, independent from outcome imputation) and adherence information (all combinations of categories for

a) days 1-3: no missing doses, 1-3 missing doses, 4-6 missing doses and

b) days 4-5: no missing doses, 1-2 missing doses, 3-4 missing doses,

unknown dosing information will be conservatively imputed as “not taken” for the 3 day arm and similar to patients where dosing is available for the 5-day arm). We will then randomly select one episode from the corresponding subset with complete information and use its values to replace the entire episode with missing outcome data.

We will repeat this process for each episode missing outcome data and calculate failure rates for both treatment arms using the imputed outcome. We will repeat this 20 times and determine the mean failure rates for each treatment arm. The difference between the mean failure rates will be calculated. Noninferiority bounds as listed in 7.2 will be consulted.

1. **SENSITIVITY ANALYSIS**

We will perform sensitivity analyses to assess how our results might change if the imputation assumptions are changed in a reasonable way, informing the robustness of the primary analysis result. We will perform complete case analysis as one form of sensitivity analysis.

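### At 9.7% versus 8% the 95% CI reaches 12.25%, so the example in protocol 4.5 and all final-look limits in SAP Table 1 are slightly too lenient, and the 64.8% power at a 4% rate is overstated

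*Combined protocol and SAP*

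**What the plan says.** Protocol 4.5 bases power on an analysis "with 1,900 children (950 per treatment arm) for the primary analysis" and a margin of 1.5 times the 5-day rate. It states 88% power when both rates are 8%, and power that "ranges from 64.8% if the failure rates in both groups are 4%, to 96.5% if the failure rates in both groups are 12" per cent. It then says that, with 8% on 5 days, "at the final analysis the 95% confidence interval would exclude 12.0%, even if the failure rate is as large as 9.7% in the 3-day" group. The 9.7% example recurs in the figure notes of protocol 5.1 and SAP 7.2.

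SAP 7.2 gives the design: "We assumed a one-sided test with an alpha=0.025, sample size = 1900 (assuming 5% loss to follow-up in each of the arms"), with looks at about one third and two thirds of enrolment, O'Brien-Fleming limits for early non-inferiority and Pocock limits for early inferiority. The 8% row of Table 1 reads "8.0% | 12.0% | 5.0% | 8.5% | 9.7"%: control rate, margin, then the largest 3-day rate at the first, second and final looks. These limits are for use: "Early non-inferiority will be considered if the 3-day failure rate is lower than the rates provided in Table 1" for the 5-day rate concerned.

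For the final analysis, protocol 5.1 and the SAP's Final analysis subsection use an age-adjusted (in the SAP also site- and gender-adjusted) difference with a 95% CI. SAP section 8, after averaging the imputed failure rates and taking their difference, adds: "Noninferiority bounds as listed in 7.2 will be consulted".

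The interim section of protocol 5.1 describes the margin as "a 1.5% relative difference failure rate between treatment (3-day) and control (5-day amoxicillin"); elsewhere it is a factor of 1.5.

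**The concern.** The sentence in protocol 4.5 can be checked by hand, and it fails. The same number is the final entry in the 8% row of Table 1, so the error is more than a loose illustration. The tabled limits guide the DSMB and, on one reading of SAP section 8, the final conclusion. A limit that is too generous lets non-inferiority be claimed when the interval still contains the margin, and it takes the one-sided error above 2.5%. An overstated power at low failure rates gives false comfort if the control rate falls well below 8%.

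**Working it through.** **Inputs.** 950 analysed per arm (protocol 4.5); one-sided 0.025, looks at 1/3, 2/3 and 1, O'Brien-Fleming and Pocock shapes (SAP 7.2); margin 1.5 × the 5-day rate. SE(p3, p5) = √{[p3(1−p3) + p5(1−p5)]/950}.

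**1. Reproducing the plan's figures.** A fixed-sample calculation at equal rates gives 60.4%, 89.5% and 98% at 4%, 8% and 12%, which does not match the stated powers. A three-look design with the stated shapes, and an alternative set at 97.5% power, has a final non-inferiority constant of 1.936 and a futility constant of 2.282, sum 4.218. Taking the SE at that alternative, for 8% control:

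- Alternative: 12 − 4.218 × 1.205 = 6.92%, where 1.205 points is SE(6.92%, 8%).
- Table 1: 12 − 3 × 1.936 × 1.205 = 5.00; 12 − 1.5 × 1.936 × 1.205 = 8.50; 12 − 1.936 × 1.205 = 9.67.
- Table 2: 6.92 + √3 × 2.282 × 1.205 = 11.68; 6.92 + √1.5 × 2.282 × 1.205 = 10.29; 9.67.

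This returns powers of 64.8%, 88.1% and 96.5% and 35 of the 36 cells of Tables 1 and 2 (the other is 6.05 against 6.0). The equal-rates SE matches 16 cells and the SE at the margin 4. Neither document states the variance or the 97.5%, so this source is inferred from the fit. At the alternative the 3-day rate is below control: 2.56% against 4%, 6.92% against 8%, 11.74% against 12%.

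**2. The 9.7% example.** This step does not depend on step 1. SE = √{(0.097 × 0.903 + 0.08 × 0.92)/950} = 1.303 points. Upper limit: 9.7 + 1.96 × 1.303 = 12.25%. With 1.936 it is 12.22%. The largest 3-day rate that excludes 12% is 9.46% (9.49% with 1.936).

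**3. All final-look rows** (%, 95% CI):

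| 5-day rate | Margin | Tabled limit | Upper limit there | Largest rate that passes | Excess |
|---|---|---|---|---|---|
| 7 | 10.5 | 8.3 | 10.69 | 8.12 | 0.18 |
| 8 | 12.0 | 9.7 | 12.25 | 9.46 | 0.24 |
| 9 | 13.5 | 11.0 | 13.70 | 10.81 | 0.19 |
| 10 | 15.0 | 12.4 | 15.23 | 12.18 | 0.22 |
| 11 | 16.5 | 13.7 | 16.66 | 13.55 | 0.15 |
| 12 | 18.0 | 15.1 | 18.17 | 14.93 | 0.17 |

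**4. Interim rows**, SE at each tabulated pair, constant 1.936. First look: 4.35, 5.36, 6.40, 7.48, 8.59 and 9.71%, against tabled 4.0, 5.0, 6.0, 7.1, 8.2 and 9.4%. The tabled values are too strict, because these 3-day rates lie below control. Second look at 8%: 8.35% against 8.5%; the tabled values are too lenient, by 0.1 to 0.2 points over the six rows.

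**5. Power at equal rates.** Rebuilding the design on the equal-rates SE gives 56.7%, 86.1% and 96.4% at 4%, 8% and 12%. Keeping the tabled boundaries and changing only the operating variance gives 62.5% at 4% and 87.1% at 8%.

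**6. Error at true rates of 12% and 8%.** SE = √{(0.12 × 0.88 + 0.08 × 0.92)/950} = 1.373 points. A final look alone that passes differences below 1.7 points has error Φ((1.7 − 4.0)/1.373) = 4.7%. Over three looks, with the 8% row's differences held fixed, the error is about 4.2% (unrounded limits) to 4.6% (as tabled) if futility stops are obeyed, and about 5.6% if not. The plan is 2.5%.

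**7. Two final rules.** At 9.6% against 8% the table passes, while the unadjusted interval reaches 12.15%. With 76 of 950 control failures, the CI rule passes at up to 89 failures on 3 days and the table at up to 92.

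**The case against.** The strongest reply is that little changes in practice. Power at the planning rate moves by 2 points or less, the two final rules differ by three children in the 8% example and disagree in about 3% of trials at 8% per arm, and 4% is half the assumed rate and below every tabled row. That stands, and it limits the size of the point. It does not rescue a sentence that is arithmetically false or a row of limits that err in one direction. A 90% interval (upper limit 11.84%) or a 95% interval for the 3-day arm alone (11.58%) would exclude 12%, but the documents specify a 95% interval for the difference.

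Four stronger readings are tempting and are not supported:

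- That the DSMB's limits are lenient throughout. The first-look non-inferiority limits are too strict.
- That section 8 decides by the table. It says only that bounds are consulted, and Table 1 also has a column holding the margin itself (12.0% in the 8% row), which may be what is meant. The wording is ambiguous.
- That the error reaches 6.6% (futility stops obeyed) or 8.2% (not obeyed). Those figures arise when the tables are read at the observed 5-day rate. Much of the excess comes from ignoring sampling error in that rate, which is a separate matter. The unadjusted CI rule against 1.5 times the observed control rate itself has about 5.6% error at a single look.
- That the documents adopt a variance favouring 3 days. They state none; the close fit makes it likely.

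**Conclusion.** The CI sentence in protocol 4.5 and the six final-look limits are wrong as written, by about 0.15 to 0.25 points. This rests only on 950 per arm and an unpooled Wald interval for the difference. The second-look limits are lenient by 0.1 to 0.2 points and the first-look limits strict by 0.3 to 0.4, given the inferred constant of 1.936. Of the three powers, only the one at 4% is materially overstated: even a fixed-sample Wald test with no interim looks reaches only 60.4%. A reader might infer that the trial is underpowered; at the planned 8% it is not, and the sample size stands. Section 8 leaves room for a second final rule that would conflict with the CI rule for 3-day rates of about 9.5% to 9.7% at 8% control. The 1.5% in protocol 5.1 is a wording slip.

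**What to change.** Recompute SAP Tables 1 and 2, the figure in both documents and the 9.7% example with the SE at each tabulated pair of rates. The final-look limits become about 8.1, 9.5, 10.8, 12.2, 13.6 and 14.9%. Restate the power range with the equal-rates SE. In SAP section 8, state that the adjusted estimate combined by Rubin's rules, with its 95% CI, is the only final decision rule, and remove or define the reference to the 7.2 bounds. In protocol 5.1, replace the 1.5% with a factor of 1.5. Treating the futility limits as non-binding is optional.

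The cost is one rerun of the design program and edits to two tables, the figures and a few sentences. The stated powers and the later-look limits become slightly less favourable; the number of children does not change.
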